### Allocation concealment

This will be done using sequentially numbered opaque sealed envelopes**.** This will be done by one of the office staff in the department who is not involved in the planning and conduction of the study.

### Sequence generation

Computer-generated random numbers will be used for randomization by the primary investigator (PB). There will be no restriction or stratification. Out of 40 clusters, 20 will receive peer-led intervention and standard care. However, the other 20 clusters will receive standard care alone after randomization. Participants will be enrolled by an investigator (SD). After 1 year, the participants will be assessed in the same manner as the baseline (Fig. 1).

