### Trial design

This is a cluster randomized controlled parallel-group trial with a superiority framework. Village is a cluster in the study. Villages will be randomized to two study arms with a 1:1 allocation ratio. The participants in the intervention arm will receive a peer-led intervention model for six months in addition to standard care.

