## Methods: participants, intervention, outcome

### Study setting

The trial will be conducted in Mendhasal and Tangi block of Khurdha district of Odisha, India.

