**Fig. 3 Fig3:**
[figure not shown]
Sampling technique

*Cluster*: Forty villages will be selected randomly from the rural field practice area of AIIMS, Bhubaneswar.

*Participant*: The eligible population will be screened for hypertension, diabetes mellitus, and dyslipidaemia. The process of screening will be continued till 18 participants are recruited from each cluster.

*Baseline assessment*: A total of 720 (40*18) participants will be recruited at baseline after written informed consent. Anthropometry, blood pressure (BP), fasting blood sugar (FBS), post-prandial blood sugar (PPBS), glycosylated haemoglobin (HBA1C), lipid profile, and renal function test (RFT) will be done for all participants, in addition to interviews with NNDMS adult interview questionnaire. Standard guidelines as recommended by govt. of India will be followed for all measurements [21].

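### Allocation is called unrestricted although 20 villages per arm are fixed, and stratification by the two known administrative blocks is ruled out, so block balance is left to chance

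*Protocol article*

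**What the plan says.** In the protocol article, Trial design makes the village the unit of allocation: "Villages will be randomized to two study arms with a 1:1 allocation ratio". Sequence generation names the tool, "Computer-generated random numbers will be used for randomization by the primary investigator", and then adds: "There will be no restriction or stratification". It goes straight on to fix the totals: "Out of 40 clusters, 20 will receive peer-led intervention and standard care", and "the other 20 clusters will receive standard care alone after randomization". The abstract repeats the split as 360 participants per arm.

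Study setting places the villages in two administrative blocks: "The trial will be conducted in Mendhasal and Tangi block of Khurdha district of Odisha, India". On sampling, the article says: "Forty villages will be selected randomly from the rural field practice area of AIIMS, Bhubaneswar". It gives no number of villages per block.

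The section on data collection and management plans a difference-in-difference estimate and a multivariate adjustment for confounders. It does not list the confounders.

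**The concern.** There are two separate issues.

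- **Wording.** Unrestricted randomisation means that each village is allocated independently, so the arm totals vary. Fixing 20 and 20 is a restriction. Taken literally, the two statements cannot both hold, and a reader cannot tell which procedure will generate the list.
- **Design.** The administrative block of every village is known before allocation, and there are only 40 units. Declining to stratify is a stated choice here, not a detail left out of a condensed article. If the blocks differ in how disease control changes over the year, a chance imbalance moves the estimated effect, and the between-block variation stays in the error term unless block is modelled.

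**Working it through.** **Inputs from the article.** 40 villages, 20 per arm, 18 participants per village, two administrative blocks. From Sample size: control proportion 50%, effect 20 points, two-sided alpha 5%, power 90%, design effect 2.5, loss to follow-up 20%. **Assumed, because not given:** villages per block, and any difference between the blocks.

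**1. The plan's own figures.** 20 × 18 = 360 per arm, 720 in all. With 50% against 70%, the unpooled formula gives (1.960 + 1.282)² × (0.21 + 0.25)/0.20² = 120.8 per arm; × 2.5 = 302.1; × 1.2 = 362.5. The total is 725, within 1% of 720. The point below does not change the sample size.

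**2. Wording check.** If allocation were truly unrestricted, P(exactly 20:20) = C(40,20)/2⁴⁰ = 0.125, and P(24:16 or worse) = 0.268. A 20:20 split would arise by chance about one time in eight, so a guaranteed 20:20 must come from a restricted scheme.

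**3. Block balance with 20:20 fixed and no stratification.** If one block has B villages, the number k that fall in the intervention arm is hypergeometric: P(k) = C(B,k) × C(40−B, 20−k)/C(40,20).

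| Assumed villages per block | Best possible split of the first block | Larger imbalance |
|---|---|---|
| 20 and 20 | 10:10, 0.248 | 12:8 or worse, 0.343; 13:7 or worse, 0.113 |
| 10 and 30 | 5:5, 0.284 | 7:3 or worse (difference of 4 or more), 0.273 |
| 15 and 25 | 8:7, 0.486 | 10:5 or worse (difference of 5 or more), 0.191 |

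**4. What an imbalance does.** If the arms differ by d villages from one block, and the blocks differ by g points, the crude arm contrast shifts by g × d/20. With g = 10 (assumed), a 12:8 split (d = 4) shifts it by 2 points and a 14:6 split (d = 8) by 4 points. The planned design implies a standard error of about 20/(1.960 + 1.282) = 6.2 points, so these shifts are about 0.3 and 0.65 of a standard error.

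**5. What difference-in-difference does.** Each village is compared with its own baseline. A block gap in level that is the same at both times cancels. If the blocks differ by g in *change*, the shift is again g × d/20.

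**6. Precision.** For an end-line comparison, the variance of a village mean is about 0.25 × 2.5/18 = 0.0347. With equal blocks, a gap g contributes g²/4. That is 0.000625 (about 2%) for 5 points, 0.0025 (about 7%) for 10 points and 0.01 (about 29%) for 20 points.

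**7. If block is modelled but not stratified.** With 12:8 in one block and 8:12 in the other, the information on the arm effect is proportional to 2 × (12 × 8/20) = 9.6, against 2 × (10 × 10/20) = 10 when balanced. The covariate therefore keeps about 96% of the information after such a split.

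**The case against.** The strongest reply is that the contradiction is one of terms. Read together, the sentences describe a random draw of 20 villages from 40 without matching or covariate constraints, and nobody would be misled about the arm sizes. That largely stands: the repair is to name the method.

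It also stands that unstratified randomisation is valid, that a correct village-level standard error already reflects chance imbalance, and that the article gives no evidence that the two blocks differ. Stratifying is an improvement on a legitimate design.

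Three stronger readings are tempting, and the article does not support them.

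- **That the arms may end up unequal in size.** The 12.5% and 26.8% in step 2 belong to coin-flip allocation. The plan fixes 20 per arm, so these figures show only that the wording is wrong and measure no risk to this trial.
- **That a block imbalance passes straight into the effect estimate.** The stated estimator is difference-in-difference, which removes a stable additive gap in level. Only a gap in change remains.
- **That block is ignored in the analysis.** Adjustment for confounders is planned without a list, which may properly sit in an analysis plan that is not shown. Block is unnamed, not excluded.

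What the reply does not answer is that the plan positively rules out a free safeguard on a factor known in advance, with only 40 units.

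**Conclusion.** The point holds as a cheap improvement. The description of the allocation is internally inconsistent and should name the scheme used. Ruling out stratification leaves balance on block to chance: about 34% of draws give 12:8 or worse if each block has 20 villages, and about 27% give a difference of four or more villages if the blocks have 10 and 30. Both block sizes are assumptions.

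The consequence is uncertain and may be modest. It depends on a between-block difference in change that the article does not report. At an assumed 10 points, a 12:8 split moves the estimate by 2 points against a planned effect of 20. The article gives no ground for calling the randomisation biased or invalid.

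**What to change.** **If the list has not been drawn**, replace the sentence on restriction with wording such as: villages will be randomised 1:1 within each of the two administrative blocks, with 20 villages per arm overall; where a block has an odd number of villages, its arms will differ by one. This is always feasible: 40 is even, so the blocks are both even or both odd, and with 15 and 25 the split would be 8:7 and 12:13. Include block as a fixed effect in the primary model, so that the analysis uses the stratification.

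**If the list has already been drawn**, do not redraw it. State the method actually used (for instance, a random draw of 20 villages from 40) and prespecify block as a covariate. This is a real possibility: Trial status gives recruitment from 1/12/2023 to 30/01/2024, the article appeared on 3 January 2024, and it does not say when villages were allocated.

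**Cost.** One sentence in the protocol, and one degree of freedom out of 38 (40 villages less two arms). The sample size stays at 720.

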**Fig. 1 Fig1:**
[figure not shown]
CONSORT flow diagram

### Intervention

The model will have six sessions (Fig. 2). The intervention will be delivered monthly through trained community health workers supervised by a physician. The sessions will be based on the following six domains: (1) NCDs self-care, follow-up care, risk factors and complications, (2) improving adherence to pharmacotherapy (linking with govt. hospital and/or janaushadhi), (3) community engagement for improving lifestyle modifications (physical activity and diet in NCDs), (4) importance of limiting substance use in NCD management, (5) Stress management, mental health, and yoga, (6) addressing other co-morbidities (cardiovascular conditions, hypothyroidism, cancer screening, etc.). Each peer group in the intervention arm will be provided with a glucometer with glucostrips and a sphygmomanometer. Peer groups will be encouraged to meet fortnightly. The participants will discuss with each other the challenges faced related to domains of intervention and seek appropriate guidance in monthly scheduled peer-led sessions. Through peer education “sharing experiences and learning among people with something in common”, the participants will be empowered to monitor blood pressure and blood sugar and identify feasible interventions for the peer group and individual level. Participants who adhere to lifestyle modifications and pharmacotherapy will be appreciated and share their stories with their peers. At the end of 1 year, intervention participants and the control group will be assessed again. Then the baseline and end line will be compared at individual and cluster levels. The participants in the control arm will receive standard clinical care at baseline [20] and be linked to the nearest govt. hospital for further follow-up care. There will be no special criteria for discontinuing or modifying allocated interventions. We are not storing samples or conducting any genetic or molecular analysis.

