### Sample size

The sample size was calculated using nMaster 2.0 software (https://www.cmc-biostatistics.ac.in/nmaster/) with the formula for cluster study design:

$$n=\frac{{\left({z}_{\frac{\alpha }{2}}+{z}_{1-\beta}\right)}^2\left[{p}_1\left(1-{p}_1\right)+{p}_2\left(1-{p}_2\right)\right]\left[1+\left(m-1\rho \right)\right]}{{\left({p}_1-{p}_2\right)}^2}$$where *p*1 = proportion of outcome in the experimental group

*p*2 = proportion of outcome in the control group

*α* = level of significance

1-*β* = power

*ρ* = Intra-cluster correlation coefficient

*m* = size of the cluster

Considering the proportion of outcome in the control group as 50%, an alpha of 5%, power of 90%, effect size of 20%, design effect of 2.5 and loss to follow-up as 20%, the estimated sample size was 720 participants (40 clusters with 18 participants in each cluster) (Supplementary file 01).

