### Data collection and management

Data will be collected in epicollect5 and analysed using Statistical Package for Social Sciences (SPSS) Version 25 (IBM Corp.). Department of Community Medicine and Family Medicine, All India Institute of Medical Sciences, Bhubaneswar, had more than 10 years of experience for data collection and data management in various studies which includes national and international collaborative studies and various trials. The standard guidelines will be followed for data entry, coding, and storage. Categorical variables will be presented as percentages or proportions. Continuous variables will be presented as mean and standard deviation. Intention to treat analysis will be done to evaluate the effectiveness of peer-led intervention compared to standard care. The multivariate analysis will be performed to adjust for confounders. For missing variables, the replacement will be tried, if essential, based on the characteristics and quantiles of the variables. There won’t be any interim analysis and no formal trial-stopping rule, as this is a behavioural intervention study with no anticipated problems detrimental to the participant.

The effect of the peer-led intervention will be estimated by Difference in Difference (DID) analysis. A *p*-value of less than 0.05 will be considered statistically significant.

The outcome assessor is not aware of the link with intervention. At the end of one year (12 months) following *outcomes* will be assessed:Improved control status of Non-communicable diseases (hypertension and/or diabetes mellitus and/or dyslipidaemia) in the intervention arm compared to the standard care arm.Mean reduction of blood pressure in the intervention arm compared to the standard care arm.Mean reduction in HbA1C among diabetes mellitus patients in the intervention arm compared to the standard care arm.Mean reduction of blood cholesterol in the intervention arm compared to standard care.

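### Forty villages are randomised, but the stated effect analysis has no village term and does not say whether the individual-level or the village-level comparison decides

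*Protocol article*

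**What the plan says.** **Design.** Under Trial design: "Village is a cluster in the study" and "Villages will be randomized to two study arms with a 1:1 allocation ratio". Under Sequence generation: "Out of 40 clusters, 20 will receive peer-led intervention and standard care"; the other 20 receive standard care alone.

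**Size.** Under Sample size, the control proportion is 50% and the other inputs are "alpha of 5%, power of 90%, effect size of 20%, design effect of 2.5 and loss to follow-up as 20" (per cent). The result is 720 people, 18 in each of 40 villages. The formula carries an ICC term, but no ICC value is given.

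**Analysis.** Data collection and management names SPSS 25, intention to treat and a 0.05 threshold. On the model it says "The multivariate analysis will be performed to adjust for confounders" and "The effect of the peer-led intervention will be estimated by Difference in Difference (DID) analysis". Neither sentence mentions village, and neither says at what level the DID is run.

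**Level of comparison.** The one statement on this is in the Intervention section: "Then the baseline and end line will be compared at individual and cluster levels".

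**The concern.** The sample size treats people in the same village as clearly correlated. The analysis text, as far as it goes, does not carry that through. It commits to two comparisons at different levels under a single significance threshold, with no rule for which one is the effect test. Because the individual level is named separately from the cluster level, a natural reading of it is a comparison of people. Unless village enters that comparison, its standard errors are too small for the design that was sized.

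Differencing does not settle the matter by itself. It removes only the part of a village effect that is the same at baseline and at one year. Monthly group sessions, fortnightly peer meetings and a glucometer and sphygmomanometer shared by each peer group could make people in one village change together. At stake is the main claim of effectiveness: as written, either p-value could be presented as the result for each of the four outcomes, and the two need not have the same error rate.

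**Working it through.** **Inputs from the article.** 20 villages per arm, m = 18, two-sided alpha 5%, power 90%, control proportion 50%, design effect (DE) 2.5, loss 20%. I read the 20% effect size as 20 percentage points (70% against 50%).

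**The plan's own figure.** Per arm before clustering: (1.96 + 1.2816)² × [0.7 × 0.3 + 0.5 × 0.5] / 0.2² = 120.8. Times 2.5 = 302.1. Times 1.2 for loss = 362.5. Two arms give 725, which agrees with the stated 720 to within rounding to 40 × 18. So the design effect of 2.5 really does drive the size.

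**Implied ICC.** From DE = 1 + (m − 1) × ICC: ICC = 1.5 / 17 = 0.088.

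**Endline-type comparison that ignores village.** True error = 2 × [1 − Φ(1.96 / √DE)].

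| Per village | DE | True error | Simulated, individual test | Simulated, t-test on village means |
|---|---|---|---|---|
| 18 | 2.50 | 21.5% | 21.6% | 4.97% |
| 14.4 (after 20% loss) | 1 + 13.4 × 0.088 = 2.18 | 18.5% | 18.1% (14 per village) | 4.96% (14 per village) |

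The simulations used 20,000 replicates, 20 against 20 villages and a normal outcome.

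**Individual change scores that ignore village.** Two correlations are needed that the article does not give: the village effect across time (CAC) and the individual residual across time (IAC). Then

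ICC of change = (1 − CAC) × 0.088 / [(1 − CAC) × 0.088 + 0.912 × (1 − IAC)].

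At 14.4 per village:

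| IAC (assumed) | CAC (assumed) | ICC of change | True error |
|---|---|---|---|
| 0.5 | 0 | 0.162 | 27.1% |
| 0.5 | 0.8 | 0.037 | 10.9% |
| 0.3 | 0.8 | 0.027 | 9.3% |
| any below 1 | 1.0 | 0 | 5.0% |

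Taking the ICC of change directly, at m = 18, values of 0.01, 0.02 and 0.05 give DE 1.17, 1.34 and 1.85, and errors of 7.0%, 9.0% and 15.0%. Together this is the 7–27% range.

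**A pooled four-cell DID regression** (arm, time and their product, every record treated as independent) behaves differently, because it also ignores the pairing within people. The ratio of true to assumed variance is 0.912 × (1 − IAC) + m × 0.088 × (1 − CAC). At m = 14.4 and IAC 0.5 it is 0.456 + 0.254 = 0.71 for CAC 0.8 (error 2.0%), and 0.456 + 1.271 = 1.73 for CAC 0 (error 13.6%). It can miss 5% in either direction.

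**HbA1c** is analysed only in people with diabetes, so fewer per village contribute. At an assumed 6 per village and ICC 0.088, DE = 1 + 5 × 0.088 = 1.44 and the endline-type error is about 10%.

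**The case against.** The strongest reply is that this reads silence as error. The article condenses a fuller protocol, and the exact model, random effects and degrees of freedom are commonly left to a statistical analysis plan. An individual-level analysis can perfectly well contain a village random effect, and the sentence on levels may mean no more than reporting at both. That sentence also sits in the Intervention section, while the effect estimator is named elsewhere. What is visible does respect clustering: the village is declared the cluster, the size is inflated for it, and a village-level comparison is named.

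Much of this stands. A reader might infer that the effect test is fixed at individual level, that 720 people will be treated as independent, or that p < 0.05 therefore fails to hold 5%. The article supports none of these. It names both levels, gives no level for the DID, and nowhere says that village will be ignored. The error rates above are conditional on that omission; those for change scores also rest on assumed correlations, and they fall to 5% if village effects are fully stable. The design effect of 2.5 was set for a proportion and need not apply to blood pressure, HbA1c or cholesterol.

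What the reply does not remove is that the article positively commits to two levels and one threshold without saying which comparison decides. That is a rule fixed badly, rather than a modelling detail left for later.

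**Conclusion.** The point holds as an ambiguity with a material consequence, not as a demonstrated error in the test. The published text permits an individual-level comparison without village to serve as the effect test. If it did, the true two-sided error would be about 18–22% for an endline-type comparison at the plan's own design effect, and roughly 7–27% for individual change scores. For change scores it equals 5% only when village effects do not change over time. The village-level comparison that the article also names would hold about 5%.

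These figures assume equal village sizes, a two-sided test, an ICC back-calculated from 2.5 and 18, and the stated ranges for correlation over time.

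**What to change.** In Intervention and in Data collection and management, name one deciding analysis per outcome that respects the village. Either of these would do:

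- a baseline-adjusted mixed model with a village random effect and small-sample degrees of freedom, linear for blood pressure, HbA1c and cholesterol, and a suitable binary version for control status; or
- a baseline-adjusted analysis of the 40 village summaries.

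For control status the two are not interchangeable: a logistic mixed model and a comparison of village proportions estimate different quantities, so the choice should be stated with its effect measure. Add that any individual-level comparison without a village term is descriptive only.

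The cost is wording, with no new data and no change of software, since SPSS MIXED and GENLINMIXED fit such models. Confidence intervals will be somewhat wider than from an individual change-score analysis that ignores village, and the sample size already allows for clustering.

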**Fig. 2 Fig2:**
[figure not shown]
Intervention model

*Study tools*: National Non-communicable Disease Monitoring Survey (NNDMS) adult interview questionnaire, Weighing Scale, Stadiometer, Sphygmomanometer, Measuring tape and Glucometer.

*Sampling strategy* (Fig. 3)

**Fig. 3 Fig3:**
[figure not shown]
Sampling technique

*Cluster*: Forty villages will be selected randomly from the rural field practice area of AIIMS, Bhubaneswar.

*Participant*: The eligible population will be screened for hypertension, diabetes mellitus, and dyslipidaemia. The process of screening will be continued till 18 participants are recruited from each cluster.

*Baseline assessment*: A total of 720 (40*18) participants will be recruited at baseline after written informed consent. Anthropometry, blood pressure (BP), fasting blood sugar (FBS), post-prandial blood sugar (PPBS), glycosylated haemoglobin (HBA1C), lipid profile, and renal function test (RFT) will be done for all participants, in addition to interviews with NNDMS adult interview questionnaire. Standard guidelines as recommended by govt. of India will be followed for all measurements [21].

